In summary, there is evidence that craving in alcohol or cocaine-dependent individuals can be reliably elicited by exposure to images, and that craving correlates with specific activation patterns in regions of the prefrontal cortex. The activation of these regions can be imaged using fNIRS. Inhibitory control may moderate craving, and activation during inhibitory control tasks can also be imaged using fNIRS. Finally, during an acute bout of exercise, activity in the prefrontal cortex increases (at moderate intensities) and decreases (at high intensities), and acute exercise has been shown to influence both inhibitory control and craving. While the evidence for exercise in general is weaker for alcohol than for cocaine dependence, the single study to date to examine the effects of acute bouts on craving found reductions for both substances. Consequently, the aim of this study is to examine whether, following acute exercise bouts at moderate and high intensities, reduced craving and increased inhibitory control can be observed in alcohol or cocaine-dependent individuals. As the focus of this study is the potential of exercise to be integrated into treatment, individuals in treatment for their dependence, who have been abstinent for a short period, will be recruited.

Based on the state of research to date, we propose the following hypotheses:In alcohol-dependent and cocaine-dependent participants, compared to a passive control condition, a bout of moderate exercise will:reduce self-reported craving;improve behavioural performance on the Stroop test;elicit increased activity in the prefrontal cortex during the Stroop test; andbe followed by decreased activity in the prefrontal cortex during exposure to substance-related cues.

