### Statistics

Sample size is calculated a priori using G*Power 3.1 [58]. Based on effect sizes reported in previous studies [25, 40] and an alpha level set to 0.05, the initial power analysis indicates that 17 participants per group are required to reach 85% statistical power. As drop-outs have to be expected, the sample size is increased to 20 participants per group. Note that the power analysis is based on the acute effects of moderate aerobic exercise on prefrontal cortex activity and inhibitory control. The statistical analysis of collected data is performed with SPSS 23.0 (IBM Statistics, USA) for Windows. Acute effects of exercise on inhibitory control and HbO_2_ concentration are examined using a 2 (group: alcohol dependent, healthy controls) × 3 (condition: control, moderate exercise, highly intense exercise) × 2 (time: pre, post) ANOVA on reaction time and the haemodynamic response to incompatible trials of the Stroop colour–word test. Additionally, effects of exercise on cue-elicited craving and HbO_2_ concentration (neutral cues subtracted from alcohol/cocaine cues) are investigated by applying a 2 (group) × 3 (condition) × 2 (time) ANOVA. Main effects and interactions are reported. Subsequently, Bonferroni-corrected *t* tests are used to decompose any significant interactions. The level of statistical significance is set to *p* < 0.05. Data from participants who do not complete all three measurement points will not be used.

Regarding missing data, as participants who do not complete all three sessions will be excluded from the study, it is anticipated that missing data will chiefly be due to faults in the fNIRS and Stroop programming, and thus will be missing at random. For this reason, multiple imputation will be used to address this issue.

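### Holm's step-down procedure would control the same family-wise error as the planned Bonferroni follow-up tests with more power for exercise versus rest: about 4 to 14 points with three contrasts, near 0 to 8 with two

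*Protocol article*

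**What the plan says.** The Statistics section plans 2 (group) × 3 (condition) × 2 (time) ANOVAs on Stroop reaction time, HbO2 response and cue-elicited craving. For the follow-up step, "Bonferroni-corrected *t* tests are used to decompose any significant interactions". It adds that "The level of statistical significance is set to *p* < 0.05". The article does not say which contrasts form the Bonferroni family, and it gives no reason for choosing the single-step form.

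On size, "the initial power analysis indicates that 17 participants per group are required to reach 85% statistical power", and for drop-out "the sample size is increased to 20 participants per group". No numerical effect size or test is given. The section notes that "the power analysis is based on the acute effects of moderate aerobic exercise on prefrontal cortex activity and inhibitory control".

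The hypotheses at the end of the Background are contrasts with rest. The first set begins "compared to a passive control condition, a bout of moderate exercise will" and predicts lower craving and better Stroop performance. The second set predicts that intense exercise leaves craving unchanged and worsens Stroop performance.

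**The concern.** A significant interaction does not by itself answer any hypothesis, because each one compares an exercise bout with rest. The follow-up t tests give those answers, so their power matters most. Single-step Bonferroni tests every contrast at 0.05/m. Holm tests the smallest p value at 0.05/m, the next at 0.05/(m−1), and so on, stopping at the first failure. It needs no assumption about dependence, controls family-wise error at the same 0.05, and is never less powerful. With 17 to 20 people per group, the difference can be large enough to change whether a contrast is declared significant.

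**Working it through.** **Inputs from the article.** Significance level 0.05; 85% power with 17 per group; 20 per group recruited; three conditions; the predicted directions in the two hypothesis sets.

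**Assumptions, because the article does not state them.** Two-sided paired t tests on differences in pre-post change between conditions; equal variance for all pairwise differences; a family of either three pairwise contrasts or the two contrasts against rest.

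**Step 1: effect size.** The 85% figure cannot be reproduced, since no effect size or test is given. It can only be back-solved. For a paired t test, power ≈ P(T > t_crit), where T is noncentral t with n−1 degrees of freedom and noncentrality dz·√n. With n = 17, t_crit = 2.120 and power 0.85, dz = 0.774 (noncentrality 0.774 × √17 = 3.19).

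**Step 2: cost of Bonferroni for one contrast at dz = 0.774.**

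| n | at 0.05 | at 0.05/2 | at 0.05/3 |
|---|---|---|---|
| 17 | 85.0% | 75.7% | 69.5% |
| 20 | 90.7% | 83.8% | 78.9% |

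At n = 17 the correction costs 85.0 − 69.5 = 15.5 points with three contrasts and 85.0 − 75.7 = 9.3 with two. This is the ceiling on what any sharper procedure could recover at this effect size.

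**Step 3: what Holm recovers.** I simulated pre-post changes under three conditions and counted a moderate-versus-rest rejection only when the within-group condition × time F test was also significant at 0.05.

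| Pattern | Family | n | Bonferroni | Holm | Gain (points) |
|---|---|---|---|---|---|
| Opposite effects (Stroop) | 3 | 17 | 69.6% | 83.7% | about 14 |
| Opposite effects (Stroop) | 3 | 20 | 79% | 90% | about 11 |
| Moderate only (craving) | 3 | 17 | 69% | 73% | about 4 |
| Moderate only (craving) | 3 | 20 | 78.5% | 82% | about 3.5 |
| Opposite effects (Stroop) | 2 | 17 | 75.7% | 83.7% | about 8 |
| Moderate only (craving) | 2 | 17 | 74.8% | 75.0% | about 0.2 |

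Holm gains most when several nulls are false, because each rejection relaxes the next threshold. With opposite effects all three pairwise nulls are false. When only moderate exercise works, intense versus rest remains a true null and relaxes little.

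**Step 4: sensitivity to effect size (three contrasts, n = 17).** Over dz from 0.4 to 0.9, Holm's gain runs from 5.8 to 15.4 points for opposite effects and from 1.5 to 3.9 points for moderate only.

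**Step 5: error control.** Under the global null at n = 17, gated Bonferroni and gated Holm have the same family-wise error, about 3.3%. They must agree there, because both make a first rejection only if the smallest p value is at or below 0.05/3.

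**The case against.** **Bonferroni is valid and prespecified.** This stands. Nothing in the article is wrong or contradictory here, and the point concerns efficiency only.

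**The family is not defined.** This stands, and it is why results are shown for both two and three contrasts. Follow-ups could also be pre versus post within each condition, or group versus group. Holm still dominates Bonferroni in any such family, but the gains above would not carry over.

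**The gate assumed here is not the planned one.** The article plans a two-group ANOVA. If a significant three-way interaction is the gate and only patients respond, moderate-versus-rest power for the craving pattern at n = 17 is about 51% with Bonferroni and 53% with Holm, a gain of about 2 points. The gate is then the main limit. For the Stroop pattern the gain remains about 14 points (69% to 83%), because the gate is nearly always passed.

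**Readings that go too far.** A reader might infer that about 15 points of power are lost for nothing. That figure is the ceiling in Step 2. Getting close to it takes opposite effects, three contrasts and only 17 completers, all at a back-solved effect. Bonferroni also gives simple simultaneous intervals, although the article plans none.

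A reader might also infer that, with three conditions, unadjusted 0.05 pairwise tests are safe after any significant interaction. That closed-test argument needs a significant condition × time test within the group being decomposed, and the article names no such test. With the three-way interaction as gate and patients following the Stroop pattern, unadjusted tests in a healthy group with no effects gave at least one false rejection in about 12% of runs, against about 4% with Bonferroni over three. The argument also fails for pre-versus-post tests within each condition, where two nulls can remain true and family-wise error reached 9.7%.

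Finally, a Bonferroni correction over six pairs in two groups (58% power at n = 17) should not be compared with Holm over three. The six-pair correction also protects across groups.

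**Conclusion.** The point holds as a modest efficiency improvement. That Holm is at least as powerful as Bonferroni over the same family, at the same nominal 0.05, does not depend on any assumption made here. The size does. It rests on dz = 0.774, two-sided paired tests, the assumed family and a within-group gate. On those terms the three-contrast gain for moderate versus rest is worthwhile for the Stroop hypotheses and small for craving. If the family is only the two contrasts against rest, there is almost nothing to gain for craving. The documents do not support calling the planned method an error, or treating the best-case gain as typical.

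**What to change.** In Statistics, replace the Bonferroni wording with: *Holm-adjusted paired t tests on the pre-post change between conditions*, applied to the same family of contrasts, and name that family. The trial status is ongoing with recruitment incomplete, and the Ethical approval section already provides for registering modifications. Because the investigators are not blinded, register the change before any results are examined.

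The cost is one sentence and an ordering of p values; no extra data or participants are needed. Holm does not give simple simultaneous confidence intervals, but ordinary 95% intervals can be reported alongside.

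Unadjusted 0.05 pairwise tests among the three conditions should be used only if a condition × time test within the group being decomposed is added to the plan and is significant. A significant three-way interaction alone is not a sufficient gate.

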### Dissemination of results

Only the investigative team will have access to the trial dataset. Results of the trial will be communicated to participants following completion of the study upon request. Individual results will not be made available. Physicians from the clinics involved in recruiting the patients will be informed about the results, and upon request the investigators will present these at faculty meetings. Findings from the study will be published in peer-reviewed academic journals.

## Discussion

To date, it has been shown that a maximal exercise test leads to reduced alcohol or cocaine craving, but not improvements in inhibitory control, when the inhibitory control test is taken during exercise [29]. Using fNIRS is a potentially promising method of imaging neural activity during both craving and inhibitory control tasks, and may provide more information about the mechanisms of exercise than craving self-report and test performance alone [23]. Furthermore, if found to be a reliable method, fNIRS can be much more easily employed in clinical practice than fMRI and EEG.

Positive effects of acute exercise bouts on alcohol craving have been reported elsewhere. Ussher et al. [59] found that 10 min of moderate cycle ergometry led to reduced craving compared with non-exercising controls, although, interestingly, differences disappeared following exercise. A finding of reduced craving following either exercise condition in the present study might therefore be an initial indicator of the duration required to elicit effects. There is no second study, to the best of our knowledge, addressing exercise and cocaine craving; a pre-clinical study assessing cocaine-seeking behaviour in rats found that 2 h of wheel-running, compared to no exercise, led to significant reductions [60].

The entirety of the literature on exercise (both acute and long-term interventions) as a treatment for alcohol dependence [34, 61] is somewhat less positive than that for illicit drugs [33, 62] and nicotine [63], although it must be noted that high-quality studies are still lacking for all substances. However, regarding cocaine specifically, the sole study to differentiate this substance from an umbrella term of “various drugs” is that of Grandjean da Costa et al. [29]. The findings of the planned study may be a further contribution towards developing studies and programmes aimed at targeting specific substance use disorders, one of the next steps in the research on exercise in this field. It will also be important to address the question of why exercise for alcohol dependence has so far yielded mixed results; is a reduction in craving indeed so short-lived that it stops immediately after exercise, or is even a longer-lasting reduction not sufficient to impact on changes in consumption?

A key aspect of the current study is the question of whether inhibitory control moderates the effects of exercise on craving. Despite research indicating that exercise at moderate intensities improves performance on inhibitory control tasks, such as the Stroop test, Grandjean da Costa et al. [29] reported no significant improvements. A non-significant trend towards improvement was reported; and, as already noted, participants in that study performed the Stroop test while exercising. The pattern of results shows that, descriptively, participants’ best performances were achieved at baseline, although one would expect improvements over repeated measurements, especially while exercising at a moderate intensity [64, 65]. It may be that, when participants are not trying to complete both exercise and the test, results at moderate intensities improve; however, this study did report reductions in craving, so until different permutations of the exercise/inhibitory control test combinations are tested, any commentary is merely speculation. We believe that in spite of this finding, the literature on both exercise improving inhibitory control and inhibitory control being associated with substance use disorders is robust, and therefore warrants exploration with new study protocols.

Already noted, and decisive in the formulation of our hypotheses, is the fact that no study to date has compared separate exercise bouts at clearly defined intensities with the goal of eliciting their effects on craving for alcohol or cocaine. Consequently, it cannot be determined whether any type of exercise is enough to affect craving, or whether reductions are the result of particular intensities. Such an investigation has been carried out for methamphetamine, with the result that both moderate and intense exercise bouts reduced craving equally during and 50 min after exercise, and to a significantly greater degree than light or no exercise [66]. However, immediately after exercise, craving was lower following the intense bout than the moderate bout. The test of inhibitory control, completed 20 min after exercise, showed the fastest reaction times following the moderate bout. An assessment of inhibitory control immediately after exercise in this study might have shed more light on the role of inhibitory control in craving; we have therefore designed our study so that craving self-report and fNIRS assessment always take place immediately prior to the Stroop test.

A final key issue that this study aims to shed further light on is the value of fNIRS assessments in addiction treatment. In the past 2 years, this technique has been used in the assessment of anxiety in heroin users [67], working memory in ecstasy users [68] and investigations of gambling [69] and Internet addiction [70]. While the simplicity, cost-effectiveness and lack of physical restrictiveness noted earlier are all attractive features of the device, it must be recognised that the bulk of the limbic system, which plays a crucial role in substance addiction [71], cannot be imaged using fNIRS. In order to maintain reasonable signal-to-noise ratios, only cortical brain activity (2–6 mm into cerebral tissue) can be mapped using fNIRS. Furthermore, recent research on the fNIRS methodology suggested that systemic changes in the extracerebral and intracerebral blood flow might compromise the interpretation of measured fNIRS signals (which is also true for other haemodynamic-based techniques such as fMRI) [72]. However, with a thorough experimental design and precise instructions to the study participant, these potential confounding factors can be kept to a minimum. Through its advantages especially in applications that require high ecological validity, and due to its high level of consistency with traditional neuroimaging techniques, fNIRS has a great potential to expand our knowledge on the functional organisation of the brain [73].

### Trial status

Ongoing. Patient recruitment incomplete.
